### Setting

This trial will be conducted in approximately 200 schools located predominantly in New South Wales, Australia. The school system in Australia is divided into three main school types: government schools, independent schools and Catholic schools. Schools from each of these groups will be recruited into the study. Schools across metropolitan, regional and rural locations will be invited to participate in order to generate a demographically representative sample. Similarly, schools with differing indices of community socio-educational advantage (ICSEA) will be targeted. If recruitment targets are not met, schools in Australian states outside New South Wales will be invited to participate. Recruitment is broadly aligned to the academic calendar, with delivery occurring during Term 2 (April) and Term 3 (July) such that assessment sessions take place during the school calendar year and risk issues can be addressed without delay. The first trial recruitment wave will be conducted primarily in independent schools in metropolitan Sydney and the Central Coast for reasons of convenience. The second and third waves will include both metropolitan and non-metropolitan sites, and include government, Catholic and independent schools. Trial management will take place at the Black Dog Institute, a translational research institute located in Sydney, Australia that is affiliated with the University of New South Wales (UNSW).

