#### Trauma Behavioural Risk Factor Surveillance System—Adverse Childhood Experience Module

The Trauma Behavioural Risk Factor Surveillance System—Adverse Childhood Experience Module (BRFSS-ACE) [79] consists of 11 items that assess exposure to nine types of adverse childhood experiences in the first 18 years of life, including: verbal abuse, physical abuse, sexual abuse, household mental illness, household alcohol abuse, household drug abuse, domestic violence, parental separation/divorce and incarcerated family members. The responses are dichotomised to indicate exposure and summed to create an ACE score ranging from 1 to 8 for each subdomain, with higher scores indicating greater exposure. Previous studies have demonstrated that this instrument has adequate internal consistency and validity [80, 81]. In this trial, the complete BRFSS-ACE will be administered at 48-month follow-up when participants are near 18 years of age. A modified version of the questionnaire consisting of eight items will be administered at baseline when participants are approximately 13 years old. This modified scale excludes items on physical and sexual abuse, and includes additional items assessing out-of-home or foster care and feelings of endangerment or physical harm.

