### Participant risk management protocol

An independent Data and Safety Monitoring Committee (DSMC) has been established to monitor the quality of trial data and the safety of research participants. The DSMC will be responsible for safeguarding the interests of participants through regular monitoring, including participant safety and adverse events. This group will be responsible for monitoring the efficacy of the interventions being tested on primary outcomes, as well as the overall conduct of the study, including recruitment, protocol compliance, accuracy and completeness of data collection. This group will also provide recommendations with respect to continuing, modifying or terminating the trial, on the basis of feasibility or safety concerns, and will have access to unblinded data. This group can recommend the trial team be unblinded if there are serious safety concerns and meets every 6 months to review trial conduct. There is no anticipated harm from this trial, as it involves a population-based sample and evidence-based interventions. However, should there be any unanticipated harms, this will be monitored by the DSMC, who will provide recommendations about care for affected participants.

All students involved in the trial will be assessed for suicidal thinking and behaviour at each assessment point, using the SIDAS and the YRBS. If participants indicate serious suicidal thinking, plans or behaviour on study surveys, an alert will be triggered whereby the research team and school counsellor are notified immediately using a purpose-built study portal. School counsellors will then follow-up with students within 48 h to offer immediate support, or refer on when necessary, which is recorded in the portal. The research team will monitor this portal and directly contact any counsellors who have not indicated follow-up with students. If students have changed or left schools, parents will be notified. At the 48-month assessment point, when students are in their final year of school, they will also be asked about history of sexual abuse. If students indicate an experience of sexual abuse, this same process of notifying the school counsellor will be followed, and schools will assume the duty of care for mandatory reporting requirements. This information will be communicated to relevant university and school ethics committees, as well as the DSMC following each assessment point.

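### At 60 months nearly all participants have left school, and the only stated action for leavers who trigger a suicide-risk alert is to notify parents, with no contact with the participant

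*Protocol article*

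**What the plan says.** The section on participant risk management in the protocol article sets out one chain of action.

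- Screening: "All students involved in the trial will be assessed for suicidal thinking and behaviour at each assessment point, using the SIDAS and the YRBS". Table 1 ticks both instruments at 60 months.
- Alert: on serious suicidal thinking, plans or behaviour, "an alert will be triggered whereby the research team and school counsellor are notified immediately using a purpose-built study portal".
- Response: "School counsellors will then follow-up with students within 48 h to offer immediate support, or refer on when necessary". The research team watches the portal and chases counsellors who have not recorded a follow-up.
- Exception: "If students have changed or left schools, parents will be notified".

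The same section fixes the school stage near the end of the trial: "At the 48-month assessment point, when students are in their final year of school". One further survey follows, at 60 months.

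**The concern.** The only timed, professional response in the article depends on a school counsellor, and so on the participant being at a participating school. The leaver rule reads as a provision for pupils who move or drop out during the trial. At the last survey, however, it would cover nearly everyone.

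Followed as written, the 60-month survey asks young people about suicidal thoughts, plans and attempts. The only action it then states towards a respondent's circle is a message to a parent, even where the respondent is an adult. No one is named to contact the person who made the disclosure. What is at stake is participant safety, not the validity of the treatment comparison.

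**Working it through.** No sample-size or error-rate figure bears on this point. The check is of the timeline and of which rule applies at each stage.

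**1. School stage.** Entry is in Year 8 (Participants).
- 24 months: Year 8 + 2 = Year 10, which agrees with the section on sexual behaviour.
- 48 months: Year 8 + 4 = Year 12, which agrees with "At the 48-month assessment point, when students are in their final year of school".
- 60 months: one year after the last school year.

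Table 1 fits this: school connectedness is collected up to 48 months and not at 60.

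**2. Calendar, using the planned wave starts (Trial design).**

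| Wave | Start | Last school year | 60-month survey |
|---|---|---|---|
| 1 | July 2019 | 2023 | July 2024 |
| 2 | April 2020 | 2024 | April 2025 |
| 3 | July 2020 | 2024 | July 2025 |

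In each wave the survey falls in the calendar year after school ends. Anyone who repeated a year is an exception, hence essentially all rather than all.

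**3. Age at 60 months, from each age that the article gives.**
- Participants section: 12–14 at entry, + 5 years = 17–19.
- Trauma module at baseline, "will be administered at baseline when participants are approximately 13 years old": about 13 + 5 = about 18.
- Sexual behaviour section: 15–16 at 24 months, + 3 years = 18–19.
- Trauma module at 48 months, "administered at 48-month follow-up when participants are near 18 years of age": near 18 + 1 = near 19.

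With 18 taken as adulthood and entry ages of 12–14, the adult share at 60 months is 1 minus the share aged 12 at baseline. The article does not give that share. If it is assumed to be 0%, 20%, 33% or 50%, the adult share is 100%, 80%, 67% or 50%. The 50% case sits poorly with a baseline age of about 13. Under any of these values, many respondents are adults.

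**4. Screening occasions.** Table 1 ticks the SIDAS and YRBS at baseline, post Stage I, and 12, 24, 36, 48 and 60 months, which makes 7. The leaver rule covers essentially all respondents at 1 of these 7. It also covers anyone who changed or left school earlier.

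**5. What the rules provide, side by side.**

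| | Still at a participating school | Changed or left school |
|---|---|---|
| Research team alerted | Yes, immediately | Yes; the alert does not depend on enrolment |
| Professional contact with the participant | School counsellor | None stated |
| Time limit | 48 h | None stated |
| Parent notified | Not stated in this chain | Yes |
| Research team's stated task | Chase the counsellor | None that fits, as no counsellor is in the chain |

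The research team knows of the alert, but its one stated task has no object once there is no school counsellor.

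**The case against.** The strongest reply is that this is a journal article. It gives risk handling a few sentences, and the full protocol is available on request. Contact steps for leavers and adults are the sort of detail that an article leaves out. The leaver sentence says that parents will be told, not that nobody else will act, and the research team receives every alert at once. The Trial design section lets data from each assessment prompt protocol changes, and Ethics and dissemination provides annual reviews and an amendment route. The last survey comes after several such reviews.

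Part of this stands. The full protocol may contain further steps, and the routes for change are real. But the article is not silent here. It states a rule for leavers, and that rule fits a scheduled survey badly. Routes for change permit a correction without making one. Reports to the ethics committees and the DSMC after each assessment point are oversight and do not answer an individual alert.

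A reader might go further in three ways that the article does not support.

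- **That the response at 60 months is slower.** The team is still alerted immediately. The stated response is less direct, but delay is not shown.
- **That the Setting section is contradicted.** It says "assessment sessions take place during the school calendar year and risk issues can be addressed without delay", but that sentence explains the timing of recruitment and delivery. It is not an undertaking about a survey held after school.
- **That telling parents of adult participants breaches consent, or should stop.** The consent terms are not shown. Ending the default could also remove a safety net when the participant cannot be reached.

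**Conclusion.** The point holds and should be fixed. At the last of seven scheduled suicide screenings, the exception for leavers becomes the rule for essentially every respondent. Its only stated action is to notify parents. Respondents are then about 17 to 19, and many are adults.

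The conclusion rests on the article's own school stages and ages, on few participants repeating a year, and on the leaver sentence being applied as written. It would fall away if the full protocol already sets out direct contact for leavers. The number of alerts at 60 months cannot be derived, because the article gives neither a retention rate for that survey nor an alert rate. The 12-month primary endpoint and its analysis are not affected.

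**What to change.** 1. Limit the counsellor and 48 h statement to students still at a participating school.
2. For any alert from a participant who has left, including all 60-month alerts, add direct contact with the participant. Assign it to a designated, suitably qualified existing role in the research team, within a stated time (for example 48 h). The alert portal and the mobile number used for login already exist.
3. Make this contact additional to the current parent notification. Whether parents of those aged 18 or over are still told by default is for the sponsor and ethics committee to decide under the consent terms.
4. Have this in place before the 60-month items open.

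The cost is an ethics amendment and some research-team time. The amount of time cannot be estimated from the article. Wave 1, planned as 12 of about 200 schools (12/200 = 6%), reaches 60 months first and would give a small first run.

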### Data collection and management

All research data collected in this trial will be stored using a unique participant ID code. A list of identifiable participant information associated with each ID code will be stored separately from the research data. The privacy, security and ownership of the research data will be maintained, and re-identifiable data will not be stored or accessible by another organisation. Access, storage and transmission logs will be recorded and regularly reviewed for anomalies. Annual audits will be conducted by the trial data manager to ensure compliance with data security processes outlined by UNSW and Black Dog Institute.

The data that will be collected include questionnaire data, mobile phone data and linked data. Coded questionnaire outcome data will be stored securely on the Black Dog Institute online research platform until ready for export. The research platform is stored on UNSW servers and supported by enterprise access controls and 256-bit encryption or higher. Data will be exported from the research platform into Microsoft Excel following assessments so that they can be checked by the data manager for data quality and accuracy. After checking, data will be exported into appropriate statistical software for analysis. Data collected by mobile phone apps will be encrypted and transmitted to a secure database hosted by Google Cloud Services in Australia. Data will be securely removed and transferred on a scheduled basis to UNSW servers by the trial data manager. Access to Google Cloud Services and the UNSW server will require authentication and will be restricted to the data manager and named members of the research team. The data manager will be responsible for extracting and securely transferring data to the research team. Only researchers whose analyses require access to the specific dataset collected from each questionnaire, app and linkage data source will be able to access those data. Linked datasets will be subject to the requirements set out by linking agencies for storage on UNSW servers using the already outlined procedures.

### Analysis

#### Primary outcome

Analysis of the primary outcome will be undertaken using an intention-to-treat approach including all participants randomised regardless of intervention received, controlling for baseline differences when appropriate. The primary analysis will be conducted using planned contrasts comparing a change in depression scores on the PHQ-A from baseline to 12 months between the trial arms (SPARX intervention vs. control), using a mixed-effects model repeated-measure analysis (MMRM). MMRM is preferred due to the ability of this approach to include participants with missing data without using discredited techniques such as last observation carried forward [87, 88]. School will be included as a random effect to evaluate and accommodate clustering effects. Variables used in determining allocation balance will be evaluated and retained in analyses where they are significant or quasi-significant. An unconstrained variance–covariance matrix will model within-individual dependencies. Transformation of scores, including categorisation, may be undertaken to meet distributional assumptions and accommodate outliers.

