### Sample size

Separate sample size estimates were derived to determine the numbers of participants needed to meet the aims of each trial stage. Power was set at 0.80, α = 0.05 (two-tailed), and a correlation of 0.5 assumed between baseline and endpoint symptom scores. To account for possible clustering effects at Stage I (i.e., participants from the same school having prognostically relevant characteristics and outcomes more alike than between schools), a design effect [84] was calculated assuming an intraclass correlation coefficient (ICC) of 0.03 (based on previous school-based studies) [85] and a cluster size of 50 students, yielding a design effect of 2.47. In order to detect a mean standardized difference of 0.3 between conditions at Stage I, a sample of 870 participants would be needed (435 per arm). Allowing for up to 30% attrition, recruitment of 1244 participants would be required (622 per arm).

Using similar parameters for Stage II (without a design effect) would require recruitment of 368 participants in total to detect the same effect size. However, participants in this stage must meet eligibility requirements regarding elevated symptoms and failure to respond to the first-stage intervention. They must also be willing to participate. Accordingly, a scenario involving recruitment of 10,000 participants at Stage I was considered, assuming 7000 participants would have endpoint data available at 12 months (allowing for 30% attrition). Conservatively estimating 20% having PHQ-A scores ≥ 10, 25% showing a reduction due to the Stage I intervention and that 50% of those eligible to enrol at Stage II do so, 525 participants would enter this stage II, with endpoint data available for at least 368 (allowing for up to 30% attrition). This sample would enable the detection of differences in changes in symptomatology scores of comparable size to those in Stage I of the trial (*d* = 0.29).

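### As worded, the primary model does not ensure that school clustering in the tested baseline-to-12-month change is modelled, and it leaves baseline adjustment conditional

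*Protocol article*

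**What the plan says.** Protocol article, Analysis, Primary outcome. The primary analysis uses "planned contrasts comparing a change in depression scores on the PHQ-A from baseline to 12 months between the trial arms", fitted as a mixed-effects repeated-measures model. An unconstrained covariance matrix is specified, but for dependence within individuals only. Clustering has one sentence: "School will be included as a random effect to evaluate and accommodate clustering effects". Baseline enters through the phrase "controlling for baseline differences when appropriate", with neither the condition nor the method given. The next section, Secondary and additional outcomes, carries the same approach to changes from baseline to the other occasions.

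Protocol article, Sample size. The calculation has "a correlation of 0.5 assumed between baseline and endpoint symptom scores". For Stage I, "a design effect [84] was calculated assuming an intraclass correlation coefficient (ICC) of 0.03" and "a cluster size of 50 students, yielding a design effect of 2.47". The result is 435 analysed per arm (870 in total) for a standardised difference of 0.3 at 80% power, and 1244 recruited after allowing for 30% attrition.

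**The concern.** The contrasts run from baseline to later occasions, so baseline reads most naturally as one of the repeated measures. A school effect that takes the same value at every occasion is then subtracted out of each student's change. It describes stable differences in level between schools but adds nothing to the standard error of the tested contrast. What matters for that contrast is how far schools differ in their change. The unconstrained within-person matrix cannot supply this, because it treats students of one school as independent once the school effect is removed.

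Such variation is plausible here. Under Procedure and participant timeline, schools must schedule four in-class sessions and may hold up to seven. Under strategies to enhance adherence, staff give reminders and encouragement. A response shared within a school is school-by-time variation.

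The two sections also sit badly together. The sample size assumes that clustering multiplies the variance of the Stage I comparison by 2.47. The model, read plainly, multiplies it by 1. If the first is right, the primary confidence interval is too narrow.

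A second, smaller matter is that baseline PHQ-A is collected from everyone and is assumed to correlate 0.5 with the endpoint, yet the wording does not secure its use as a covariate.

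**Working it through.** **Inputs from Sample size:** two-sided α 0.05, power 0.80, d = 0.3, r = 0.5, ICC 0.03, 50 students per school, attrition 30%. **Not in the documents:** the correlation c between a school's effect at baseline and at 12 months. It is an assumption, shown as a range.

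**1. The plan's own figure.** Design effect = 1 + (50 − 1) × 0.03 = 2.47. Variance of a change score (unit SD) = 2(1 − r) = 2(1 − 0.5) = 1.00. A t-based two-sample calculation for d = 0.3 gives 176 per arm. 176 × 2.47 = 434.7, so 435 per arm and 870 in total. 435 / 0.7 = 621.4, so 622 per arm and 1244. All stated figures reproduce. An unadjusted comparison of 12-month scores also has variance 1 and gives the same 435.

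**2. Does a constant school effect reach the tested contrast?** The generalised-least-squares standard error of the arm-by-time contrast was computed for 26 schools of 50 (650 per arm), with a school intercept and an unstructured within-person covariance.
- Complete data: 0.05547 for every school variance tried from 0 to 0.10. This is the unclustered value, √(2 × 1.00 / 650) = 0.05547.
- 30% missing at 12 months: 0.06351 at school variance 0 and 0.06326 at 0.10.

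The cancellation is exact with complete data and nearly exact with 30% missing.

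**3. What is then left out.** With school variance 0.03 at each occasion:
- ICC of change = 2 × 0.03 × (1 − c) / [2(1 − 0.5)] = 0.06(1 − c)
- ignored design effect DE = 1 + 49 × 0.06(1 − c)
- type I error = 2Φ(−1.96 / √DE)

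| c | ICC of change | DE ignored | Type I error |
|---|---|---|---|
| 1 | 0 | 1.000 | 5.0% |
| 0.9 | 0.006 | 1.294 | 8.5% |
| 0.8 | 0.012 | 1.588 | 12.0% |
| 0.5 | 0.030 | 2.470 | 21.2% |

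At c = 0.5 the ignored factor is the protocol's own 2.47. With 30% missing at 12 months the errors are 10.3% at c = 0.8 and 17.8% at c = 0.5.

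Simulation under the null (26 schools of 50, complete data, 1500 runs per setting) gave 12.1% at c = 0.8 and 20.4% at c = 0.5 for the intercept-only model. A school-level t-test of mean change in the same runs gave 5.4% and 4.5%. The 5% at c = 1 is analytic only.

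**4. Baseline adjustment.** Variance with baseline as covariate = 1 − r² = 1 − 0.25 = 0.75, against 1.00 for unadjusted change. The t-based size falls from 176 to 132 per arm. Keeping the design effect at 2.47, 132 × 2.47 = 326.04, so 327 per arm and 654 in total, against 870. Equivalently, 435 per arm is 435 / 2.47 = 176 effective participants per arm, with power 80% at variance 1.00 and 90% at 0.75.

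**The case against.** The text says only that school is a random effect. It does not say intercept-only and does not exclude a school-by-time term. If the change score itself were the response, with baseline controlled, the school effect would not cancel. The design effect in the sample size suggests that clustering in the tested contrast is meant to be modelled, and this is an article whose full protocol and analysis plan are not shown. All of that stands, and it makes the point conditional. It does not remove it: the article names the term and states that it accommodates clustering, and an analyst who followed the text literally could fit a model in which it does not.

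Three stronger inferences are tempting, and the documents do not support them:
- **That the trial ignores clustering.** Stable differences between schools are handled, and properly removed from the change. Only school-by-time variation would be missed.
- **That the type I error is above 5%.** This depends on c. If school effects are perfectly stable (c = 1), the test is valid.
- **That 435 per arm shows unadjusted change to be the planned analysis.** An unadjusted 12-month comparison gives the same number, and the text does permit control for baseline.

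On efficiency, it is fair to say that Stage I power is no constraint if 10,000 are recruited and 7000 have 12-month data, as the Sample size section considers; the gain from adjustment then matters less. Recruiting more schools does not cure the type I error, however. DE depends on students per school and the ICC of change, and 10,000 students in about 200 schools is still 50 per school.

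**Conclusion.** The concern holds in conditional form: the Primary outcome section does not ensure that clustering in the tested contrast is modelled. With baseline as a modelled occasion and a time-constant school effect, type I error runs from 5% (c = 1) through 8.5% (0.9) and 12% (0.8) to 21% (0.5). This rests on the protocol's ICC of 0.03 at each occasion, r = 0.5, 50 per school and complete data, and on a value of c that the documents do not supply. The model as plainly read also does not match the 2.47 used for the sample size.

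The conditional baseline wording is a separate and lesser matter. If adjustment is not made, variance at r = 0.5 is 1.00 instead of 0.75, so about a third more participants are needed for the same power (870 / 654 = 1.33). The test is not biased by it.

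**What to change.** Restate the primary model. Take the post-baseline PHQ-A scores as the response, with baseline PHQ-A always included as a covariate, replacing the conditional phrase. Include a school random effect on the follow-up occasions, or a school-by-occasion effect, and test the arm effect at 12 months. With baseline no longer a response, the school effect stays in the between-arm contrast and does not cancel. An alternative keeps baseline as a response with its mean constrained equal across arms; the school effect must then be allowed to differ by occasion. Carry the same wording to the secondary outcomes, and make the sample-size text name the same contrast as the model.

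The cost is model wording. No extra data are needed. The standard error may widen for clustering, which is what makes it valid, and baseline adjustment offsets part of that.
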